## Abstract

**Background:**

The outbreak of SARS-CoV-2 at the end of 2019 sounded the alarm for early inspection on acute respiratory infection (ARI). However, diagnosis pathway of ARI has still not reached a consensus and its impact on prognosis needs to be further explored.

**Methods:**

ESAR is a multicenter, open-label, randomized controlled, non-inferiority clinical trial on evaluating the diagnosis performance and its impact on prognosis of ARI between mNGS and multiplex PCR. Enrolled patients will be divided into two groups with a ratio of 1:1. Group I will be directly tested by mNGS. Group II will firstly receive multiplex PCR, then mNGS in patients with severe infection if multiplex PCR is negative or inconsistent with clinical manifestations. All patients will be followed up every 7 days for 28 days. The primary endpoint is time to initiate targeted treatment. Secondary endpoints include incidence of significant events (oxygen inhalation, mechanical ventilation, etc.), clinical remission rate, and hospitalization length. A total of 440 participants will be enrolled in both groups.

**Discussion:**

ESAR compares the efficacy of different diagnostic strategies and their impact on treatment outcomes in ARI, which is of great significance to make precise diagnosis, balance clinical resources and demands, and ultimately optimize clinical diagnosis pathways and treatment strategies.

*Trial registration* Clinicaltrial.gov, NCT04955756, Registered on July 9th 2021.

## Background

Acute respiratory infection (ARI) is one of the major diseases that threatens human health worldwide, with high morbidity, high severity and high medical costs [1]. COVID-19 [2] in 2019 and the H1N1 influenza in 2009 [3] have imposed enormous healthcare burden and economic loss worldwide. According to World Health Organization (WHO), lower respiratory tract infections (LRTI) are the fourth leading cause of death globally in 2019 [4]. Respiratory tract infections can be caused by a wide spectrum of pathogens including bacteria, viruses, fungi, mycoplasma, chlamydia, etc., with similar clinical manifestations but completely different treatment. Besides, colonization and complex infection make it more difficult to make accurate diagnosis. Once diagnosed or treated improperly, severe pneumonia will develop, which is associated with high mortality and various complications [5].

Early and precise diagnosis for respiratory pathogens is of great significance for making appropriate treatment strategies, saving healthcare resources and reducing unnecessary use of antibiotics. The gold standard is culture or isolation from respiratory specimen [6], which is time-consuming along with low positivity. Nowadays, emerging technologies, such as multiplex polymerase chain reaction (PCR) and metagenomic next-generation sequencing (mNGS), have become more and more widely used in the rapid detection of respiratory tract infections. Multiplex PCR is relatively cost-saving and can report results within hours [7], which has become the most attractive test method and currently the most commonly used method in clinical laboratory [8]. Filmarray respiratory panel (FA-RP) is featured as automated sample preparation, nucleic acid extraction and nested multiplex PCR detection, which can detect more than 20 pathogenic microorganisms in one test, including 17 respiratory viruses and 3 atypical pathogens [7, 9]. QIAstat-Dx RP is another full-automated multiplex real-time PCR test for identifying common respiratory viral and bacterial pathogens within 1 h [10]. Although diagnostic performance of multiplex PCR has been proved to be satisfying [11], detection spectrum of microorganisms is still limited, especially in rare or emerging pathogens [12]. mNGS can identify pathogens without subjective bias within 48 h [13, 14], but is more time-consuming, more expensive and requires well-equipped laboratory to perform.

Although a variety of diagnosis tools have been applied clinically, there still lacks consensus on clinical diagnosis pathway for ARI. The impact of multiplex PCR and mNGS on prognosis of ARI is still unclear. Therefore, based on mNGS and multiplex PCR detection, the study proposes a multicenter, open, randomized controlled clinical trial to compare the efficacy of different diagnostic strategies and its impact on prognosis for ARI, which ultimately aims to optimize the diagnostic pathways and treatment strategies.

## Methods

### Study design

The study is a multicenter, open-label, randomized controlled, non-inferiority clinical trial recruiting patients with respiratory tract infections who meet inclusion and exclusion criteria (Table 1). Enrolled patients were divided into two groups in a 1:1 ratio [15]: Group I will be detected by mNGS for pathogens. Group II will first receive respiratory multiplex PCR, then mNGS in severe pneumonia (Table 2) if multiplex PCR results are negative or inconsistent with the clinical conditions. Disease condition and treatment status will be followed up every 7 days until reaching predefined outcomes within 28 days. If a participant with mild symptoms become severe during follow-up, respiratory samples should be collected again for mNGS detection. The detailed research process is shown in Fig. 1.

**Table 1 Tab1:** Inclusion and exclusion criteria

Inclusion criteria	• Aged from 18 to 80 years old • Unlimited gender • Newly developed cough, expectoration, purulent sputum, or exacerbation of original respiratory diseases within 14 days • Meet at least one of the following items: (1) Fever (> 38 ℃) (2) Consolidation signs and/or wet rales on chest physical examination (3) Leucocyte > 10*10^9^/l or < 4*10^9^/l (4) Patchy infiltration or interstitial changes on chest radiology
Exclusion criteria	• Highly-suspected of or confirmed with noninfectious lung diseases (tumor, autoimmune diseases, etc.) • The pathogen has been identified • Insufficient respiratory tract or blood specimen • Unable or refusing to cooperate due to physical or psychological factors • Participating in other clinical studies • Investigators or clinicians considers unsafe for the subject to participate
Exit criteria	• Participants request to withdraw from the interview

**Table 2 Tab2:** ATS/IDSA criteria for severe CAP

***Minor criteria***
Respiratory rate ≥ 30 breaths/min
PaO_2_/FiO_2_ ratio ≤ 250
Multilobar infiltration
Confusion/disorientation
Uremia (BUN ≥ 20 mg/dL)
Leukopenia (white blood cell count < 4 *10^9^/L)
Thrombocytopenia (platelet count < 100*10^9^/L)
Hypothermia (core temperature < 36 °C)
Hypotension requiring aggressive fluid resuscitation
***Major criteria***
Invasive mechanical ventilation
Septic shock with the need for vasopressors

Respiratory rate, a need for noninvasive ventilation can substitute for a respiratory rate > 30

PaO_2_/FiO_2_, arterial oxygen pressure/faction of inspired oxygen; BUN, blood urea nitrogen; Leukopenia, as a result of infection alone

**Fig. 1 Fig1:**
[figure not shown]
Study outline. *Group I will be detected by mNGS for pathogens. Group II will first receive respiratory multiplex PCR, then mNGS in severe pneumonia if multiplex PCR results are negative or inconsistent with the clinical conditions. *CRP* C-reactive protein test, *PCT* procalcitonin, *ESR* erythrocyte sedimentation rate, *NPS* nasopharynx swab, *BALF* bronchoalveolar lavage fluid, *mNGS* metagenomic next-generation sequencing

### Ethical and confidential considerations

The study protocol and informed consent forms have been approved by the Ethical committee of Huashan Hospital affiliated to Fudan University (protocol ID: KY2021-450). The investigator will objectively and comprehensively introduce the purpose, procedure, potential benefits and risks of the study to the subjects and their legal representatives, and obtain informed consent through interview before registration. All patients will provide written informed consent.

### Site selection

This trial is led by the Huashan Hospital affiliated to Fudan University and the recruiting-cooperative units were distributed over 5 points in Shanghai: Huashan Hospital, Ruijin Hospital, Tongji Hospital, Shanghai Pulmonary Hospital, Shanghai General Hospital, Minhang Hospital and their branches. Project leader will conduct the quality control every six months. ESAR network for early identification of acute respiratory infection in Shanghai is shown in Fig. 2 [16].

**Fig. 2 Fig2:**
[figure not shown]
ESAR network. The map was acquired from: https://leafletjs.com/

### Study flowchart and clinical evaluation of enrolled participants

The following information will be collected at enrollment: baseline information, clinical history, physical examination, routine laboratory examinations (including blood routine, liver and kidney function test, electrolytes, blood coagulation tests, C reaction protein, erythrocyte sedimentation rate, procalcitonin, cytokines, etc.) and respiratory specimen culture. According to the above test results, the researchers evaluated the severity of pneumonia at the time of enrollment. 5–10ml EDTA anticoagulation and respiratory samples will be collected at enrollment (BALF ≥ 3 ml, or sputum ≥ 2 ml or more, or 2 nasopharyngeal swabs). After quality control, subjects will be randomly assigned to two groups according to the ratio of 1:1. Group I will be directly tested by mNGS, and group II will first receive multiplex PCR and subsequently mNGS according to multiplex PCR results and the severity of pneumonia. If mild pneumonia progressed to severity in subsequent follow-up, additional mNGS will be performed. Randomization was performed through an online central randomization system stratified by study site. Patients in both groups will be followed up for 28 days and a final diagnosis will be made by experienced physicians.

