### Assessment and analysis of outcomes

The primary and secondary outcomes will be compared between group I and group II. Primary outcomes are time to start targeted antibiotic therapy. Secondary outcomes include incidence of clinically significant events (oxygen inhalation, ICU admission, tracheal intubation, tracheostomy, death, etc.), clinical remission rate (Meet all the following criteria for at least 24 h: (1) Heart rate < 100 bpm; (2) Blood pressure > 90 mmHg; (3) Body temperature < 38 °C; (4) Respiratory rate < 24/min; (5) Oxygen saturation at room temperature > 90%), hospitalization length within 28-day follow up.

SPSS 20 and Prism 8.0 will be applied for statistical analysis. Firstly, whether the enrolled cases met inclusion and exclusion criteria, and whether the actual number of enrolled, excluded, and dropped cases in each center are counted will be reviewed at the end of the study. Second, demographics characteristics, baseline information, follow-up status and outcomes will be compared between two groups. Statistical methods including *t* test or Mann–Whitney test, Pearson's chi-square test or Fisher test, cox method, Kaplan-Meier survival curve, log-rank method, logistic regression models will be applied in the form of two-tailed test. *P* < 0.05 was considered statistically significant.

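### Randomisation is stratified by site but the named tests carry no site term: if sites differ, the P value is conservative and some power is lost

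*Protocol article*

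**What the plan says.** The design and analysis sections of the protocol article treat site and severity differently.

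- **Site is a randomisation stratum.** Under Study flowchart and clinical evaluation of enrolled participants: "Randomization was performed through an online central randomization system stratified by study site". Allocation is 1:1. Site selection lists "Huashan Hospital, Ruijin Hospital, Tongji Hospital, Shanghai Pulmonary Hospital, Shanghai General Hospital, Minhang Hospital and their branches".
- **Severity is known before assignment.** The same flowchart section says that "the researchers evaluated the severity of pneumonia at the time of enrollment" and places the random assignment after this step. Severity is not a stratum, but it helps to steer one arm: "group II will first receive multiplex PCR and subsequently mNGS according to multiplex PCR results and the severity of pneumonia".
- **The primary outcome is a time to event.** Assessment and analysis of outcomes: "Primary outcomes are time to start targeted antibiotic therapy".
- **The methods carry no stratum or covariate.** The same section lists t test or Mann–Whitney, chi-square or Fisher, and then "cox method, Kaplan-Meier survival curve, log-rank method, logistic regression models will be applied in the form of two-tailed test", at P < 0.05. The list is open. No method is named as primary, and none is labelled stratified or unstratified.
- **Sites are expected to differ in one respect.** The limitations in the Discussion concede that conventional specimen testing varies between hospitals, while multiplex PCR and mNGS are done in a central laboratory.

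**The concern.** Balancing the arms within site removes site-to-site variation from the true sampling variance of the treatment comparison. A test that ignores site still counts that variation as noise. Its P value is then too large on average, and power is lost. In a log-rank or Cox analysis, leaving out a factor that affects the hazard also pulls the estimated HR toward 1.

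Conventional culture is part of the work-up at enrolment and follow-up. Hospital differences in it could plausibly affect when targeted treatment starts, so a site effect on the primary outcome is credible, though the article does not quantify it.

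Baseline severity raises a lesser question. It is recorded before assignment, is probably prognostic, and helps decide who in Group II goes on to mNGS. Adjusting for it could gain some power, but no listed method is said to use it.

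**Working it through.** **The plan's own figures.** Sample size calculation gives HR 1.50, α 0.05, β 0.10, 10% additional mNGS in Group II, and 200 per group; 200 × 1.1 = 220, and 2 × 220 = 440. Schoenfeld's formula, two-sided, 1:1:

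d = 4(1.960 + 1.282)² / (ln 1.5)² = 42.03 / 0.1644 ≈ 256 events, or 128 per arm.

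Depending on how the 10% is treated, dilution raises this to about 153 to 169 per arm by the Schoenfeld or Freedman formula. The article states no event probability, so 200 can be neither reproduced nor refuted. Nothing in the calculation refers to site or severity.

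**Inputs to the simulation.** From the article: 1:1 allocation stratified by site, six listed hospitals, 400 evaluable patients, 28-day follow-up, two-sided 5% tests, HR 1.5. Assumed, because the article does not give them: exponential times with baseline hazard 0.12 per day, permuted blocks of 4 within site, sites of equal expected size, 30% severe, normally distributed site effects on the log hazard, and the severity HR. A site SD of 0.3, 0.5 or 0.8 means that a site one SD above average has a hazard e^0.3 = 1.35, e^0.5 = 1.65 or e^0.8 = 2.23 times the average.

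**Results.** Each cell gives log-rank unstratified / stratified by site / stratified by site × severity.

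| Site SD | Severity HR | Type I error | Power at HR 1.5 (%) |
|---|---|---|---|
| 0 | 1 | 0.054 / 0.054 / 0.053 | 98.4 / 97.9 / 96.8 |
| 0 | 2 | 0.052 / 0.051 / 0.052 | 96.6 / 95.8 / 97.4 |
| 0 | 3 | 0.049 / 0.051 / 0.050 | 94.3 / 93.2 / 96.5 |
| 0.3 | 1 | 0.041 / 0.052 / 0.049 | 95.8 / 97.2 / 96.5 |
| 0.3 | 2 | 0.043 / 0.052 / 0.047 | 94.9 / 95.8 / 96.5 |
| 0.5 | 1 | 0.034 / 0.049 / 0.048 | 93.8 / 97.0 / 96.3 |
| 0.5 | 2 | 0.040 / 0.056 / 0.053 | 93.0 / 95.7 / 96.5 |
| 0.8 | 2 | 0.022 / 0.047 / 0.048 | 84.3 / 94.6 / 96.5 |

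Runs per row: at least 4,000 for type I error (Monte Carlo SE √(0.05 × 0.95/4000) = 0.003) and at least 2,000 for power (SE about 0.5 point near 95%). The three tests were applied to the same simulated trials. A Cox model with treatment alone has the log-rank test as its score test, so the pattern carries over.

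**Site.** Gain from site stratification: 97.2 − 95.8 = 1.4 and 95.8 − 94.9 = 0.9 points at SD 0.3; 97.0 − 93.8 = 3.2 and 95.7 − 93.0 = 2.7 at SD 0.5; 94.6 − 84.3 = 10.3 at SD 0.8. With no site effect it costs 0.5, 0.8 and 1.1 points in the first three rows.

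**Sensitivity.** At a smaller effect, HR 1.38, the gains are about 2 points at SD 0.3, about 7 at SD 0.5 and about 17 at SD 0.8; the cost with no site effect is again about 1 point (87.3 to 86.2%). With a baseline hazard of 0.05 per day and 3,000 runs, power at HR 1.5 was 89.7 / 91.9 / 93.7% (SD 0.4, severity HR 2) and 85.0 / 90.9 / 93.8% (SD 0.6, severity HR 2.5). Unstratified type I error was 0.042 and 0.032.

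**Severity.** With no site effect and severity HR 2 or 3, the unstratified type I error is 0.052 or 0.049, so omitting severity leaves the P value intact. In the scenarios where severity matters, adding it to the site-stratified test gains about 1 to 3 points. Where neither factor matters, crossing both into 12 strata costs 98.4 − 96.8 = 1.6 points, a reason to enter severity as a covariate instead of a further stratum.

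**The case against.** The strongest objection is that this is silence and not a stated error. The list of methods is open, and it includes "cox method, Kaplan-Meier survival curve, log-rank method, logistic regression models". Cox and logistic models can hold both factors, and a condensed article may leave strata and covariates to a full protocol or analysis plan that is not shown. This largely stands. It limits the point to a request to state the choice. It does not remove the point, because the article does have an analysis section that names its tests. The t test, Mann–Whitney, chi-square and Fisher tests it names cannot carry a stratum, and a log-rank test named without qualification is normally read as unstratified.

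Five stronger readings are tempting and not supported:

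- *The article prescribes unstratified tests.* It labels no test as such and designates none as primary.
- *Omitting severity miscalibrates the P value.* Severity is not a randomisation stratum, and the simulated type I error stays near 5%.
- *The false-positive risk is inflated.* Ignoring site errs in the conservative direction.
- *Non-inferiority becomes easier to show.* An HR pulled toward 1 and a standard error that is too large can act in opposite directions. The simulations cover only a difference test, so no conclusion is drawn.
- *Sites differ in transport time to the central laboratory.* The article says nothing on this; it concedes only differences in conventional testing.

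**Conclusion.** The point holds in a limited, conditional form. The methods as named do not reflect the site-stratified randomisation, and they make no stated use of a severity assessment that is already available at baseline.

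If sites differ, an unstratified analysis is conservative (type I error about 0.02 to 0.04 in the scenarios tried). At HR 1.5 it gives up about 1 to 3 points of power at a site SD of 0.3 to 0.5, and about 10 points at 0.8. If sites do not differ, nothing is lost. Leaving out severity is purely a small loss of efficiency.

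These sizes depend on assumed site and severity effects, the share of severe patients and the baseline hazard, none of which the article gives. The trial's validity is not in question. This is a low-cost improvement that should be fixed before the data are analysed, which also prevents a later choice between adjusted and unadjusted results in an open-label trial.

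**What to change.** In Assessment and analysis of outcomes, or in the analysis plan if it does not already say so, state that:

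- the primary comparison is a Cox model stratified by study site and adjusted for baseline severity (severe versus non-severe, Table 2), with the HR, its confidence interval and its P value all from that model; if a log-rank test is also reported, it is stratified by site;
- severity is the value recorded at enrolment, not updated for patients who become severe during follow-up;
- branches are pooled with their parent hospital, so that strata do not become sparse;
- binary secondary outcomes (clinically significant events, clinical remission) are analysed by logistic regression with the same two factors.

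The cost is a few sentences. Site is held by the randomisation system and severity is already assessed at enrolment. The statistical price of stratifying by site is at most about 1 point of power if sites turn out not to differ. The simulations used a site × severity log-rank test as a stand-in for the adjusted Cox model, so that model's own power was not computed.

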### Diagnostic methods

In this study, we plan to detect pathogens in group I by mNGS, and in group II by respiratory multiplex PCR. Reports will be returned within 48 hours. The later will include 16 respiratory pathogens and 3 atypical respiratory pathogens, including coronavirus, influenza A virus, influenza B virus, mycoplasma pneumoniae, adenovirus, respiratory syncytial virus parainfluenza virus (I, II, III, IV), human metapneumovirus, haemophilus influenzae, klebsiella pneumoniae, staphylococcus aureus. mNGS assays can simultaneously cover a wide spectrum of pathogens in a single sequence, including known pathogens and emerging unknown microorganisms.

### Duration of follow‑up

All participants will be followed up every 7 days for disease status and treatment conditions since enrollment, including symptoms, signs, routine laboratory examinations, along with respiratory specimen culture. Besides, SOFA score will be evaluated every 7 days.

### Sample size calculation

PASS 11 software was applied to calculate the sample size. Assuming hazard ratio (HR) = 1.50, *α* = 0.05, *β* = 0.10, and a 10% rate of participants in Group II receiving mNGS additionally, each group requires 200 subjects. Considering a 10% rate of lost to follow-up, each group needs 200 × 1.1 = 220 subjects; therefore, the total sample size of the two groups combined is calculated to be 440 subjects.

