## Discussion

Exploring the efficiency of different diagnosis strategies is of great significance for optimizing ARI early management and prognosis. Since multiplex PCR was first applied by Chamberlian et al. to screen missing locus on Duchenne muscular dystrophy in 1988 [17], it has been successfully applied in many fields. The sensitivity and specificity of respiratory multiplex PCR has been proved to be higher than 90% [18]. Shengchen et al. [19] reported that FA-RP can shorten the length of stay and reduce antibiotic administration in hospitalized adults with lower respiratory tract infection. Similarly, our previous study [20] found that 53.8% received antiviral therapy and 69.6% received antibiotics adjustment in multiplex PCR group, while 12.7% and 5.1% in traditional examination group, indicating a positive effect on outcomes. Simultaneously, FA-RP can also lower the risk of infectious disease transmission [20]. However, Brendish et al. [21] argued that multiplex PCR was not associated with a reduction in the overall duration of antibiotic use in hospitalized adults with acute respiratory illness. Besides, multiplex PCR cannot detect rare or unknown respiratory pathogens.

Compared with traditional culture, mNGS improves sensitivity and shortens time to identify various pathogens [22]. The sensitivity and specificity in BALF samples were 88.89% and 14.86% [23], and 34% of candidate pathogens can be detected by mNGS [24] to provide more accurate diagnostic information. Furthermore, it can screen rare pathogens [25] such as COVID-19 [26] and Nocardia [27], but subject to missing detection, expensive equipment and high personnel demand. There is few studied reporting impact of mNGS on ARI prognosis. Zhang et al. [28] performed repeated mNGS testing in nine patients with suspected central nervous system infection (CNS) and found that mNGS semi-quantitative values can be used to dynamically monitor pathogen load and disease progression. Hongxia Duan et al. [29] suggested that 28-day mortality in mNGS-positive group was higher (9.0% vs 0%, *P *= 0.049), but the average survival time (176.64 vs 150.96 days, *P *= 0.425) was not statistically different, indicating that positive results were correlated with worse prognosis. However, these studies did not analyze the influence of antibiotics, which might lead to the lower detection rate by traditional methods.

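### The 10% loss is applied as ×1.1, so 440 leaves 198 per group where 200 are required; the 10% mNGS input needs justifying, and the 90% power cannot be checked from the stated inputs (minor)

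*Protocol article*

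**What the plan says.** The Sample size calculation section of the Protocol article names PASS 11 and gives these inputs: "hazard ratio (HR) = 1.50", α = 0.05, β = 0.10 and "a 10% rate of participants in Group II receiving mNGS additionally". From these it concludes that "each group requires 200 subjects". It then allows for 10% loss: "each group needs 200 × 1.1 = 220 subjects", 440 in total.

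Three other places bear on this:
- Study design describes Group II as multiplex PCR first, "then mNGS in severe pneumonia (Table 2) if multiplex PCR results are negative or inconsistent with the clinical conditions". The Abstract says the same, and the Discussion presents the trial as a comparison of PCR combined with mNGS against direct mNGS.
- The primary endpoint (Abstract; Assessment and analysis of outcomes) is the time until targeted treatment starts, with 28 days of follow-up.
- Assessment and analysis of outcomes says that the tests "will be applied in the form of two-tailed test". The sample size paragraph gives no sides for α.

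**The concern.** There are two faults in the stated text and one consequence.

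1. Multiplying by 1.1 is not the inverse of losing 10%. The printed result misses the target set in the same paragraph.
2. The mNGS given to some Group II patients is directed by the protocol. A hazard ratio comparing the two strategies already contains its effect. Listing it as a further input suggests that it was handled as crossover or contamination, in which case the calculation and the design address different comparisons. The paragraph does not say how it was used.
3. Power for a hazard ratio depends on the number of events. The paragraph counts only patients, and how many events are needed changes considerably with the handling of the 10% and the sidedness of α. If the primary result is inconclusive, a reader could not tell from the stated figures whether the trial collected the information it planned for.

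**Working it through.** **Inputs.** From Sample size calculation: HR 1.50, α 0.05, power 0.90, 10% of Group II with additional mNGS, 200 per group, 10% loss. From Study design: 1:1 allocation. The event proportions and dilution models below are assumptions, because the article gives none.

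**Loss step.**
- As printed: 200 × 1.1 = 220 per group; 2 × 220 = 440.
- Check: 220 × 0.9 = 198 per group, 396 in total.
- Correct: 200 / (1 − 0.10) = 222.2, rounded up to 223 per group; 2 × 223 = 446.
- Difference: 3 per group, 6 in total (6/440 = 1.4%).
- Effect on power (HR 1.50, two-sided): 400 against 396 evaluable gives 81.8% against 81.4% at 50% events, and 95.2% against 95.0% at 80% events. The loss is under half a point.

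**Events for 90% power (Schoenfeld, 1:1).** d = 4(z_α + z_β)² / (ln HR)².
- Two-sided 0.05: 4 × (1.960 + 1.282)² = 42.03.
- One-sided 0.05: 4 × (1.645 + 1.282)² = 34.26.

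The first row below takes HR 1.50 undiluted. The other three are possible ways in which a 10% dilution might have been entered.

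| Handling of the 10% | HR used | Two-sided events (% of 400) | One-sided events (% of 400) |
|---|---|---|---|
| None | 1.50 | 256 (64%) | 209 (52%) |
| 0.9 × 1.5 + 0.1 | 1.45 | 305 (76%) | 249 (62%) |
| 1.5^0.9 | 1.440 | 316 (79%) | 258 (64.5%) |
| 1/(0.9/1.5 + 0.1) | 1.429 | 331 (83%) | 270 (67%) |

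Freedman's formula adds 7 events to each two-sided figure, so the choice of formula matters less than the handling of the 10%.

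The plan's 200 per group cannot be reproduced, because it needs an event proportion that is not given. It is attainable under every row.

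**Power with 440 enrolled and 396 evaluable (undiluted, two-sided).** Power = Φ(½√d × ln 1.50 − 1.96). At 50% events, d = 198 and ½ × 14.07 × 0.4055 − 1.96 = 0.893, which gives 81%.

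| Event proportion (assumed) | Events | Power |
|---|---|---|
| 50% | 198.0 | 81% |
| 60% | 237.6 | 88% |
| 70% | 277.2 | 92% |
| 80% | 316.8 | 95% |

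The 256 events are 256/396 = 65% of those evaluable.

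**The case against.** The strongest reply is that this is a journal article summarising a software calculation. The event proportion and the sidedness may well stand in the full protocol, so their absence here does not make 200 per group wrong. That stands. The one certain arithmetic error moves the total by 1.4%, which also stands.

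The role of HR 1.50 is open too. The trial is called non-inferiority, and if 1.50 is a margin with a true ratio of 1, extra mNGS in Group II does not shrink it. The dilution rows then have no meaning, and 256 events suffice at one-sided 0.025. This is a fair point against using any diluted figure as the requirement. It also strengthens the case for saying what the 10% is doing in the paragraph.

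Two stronger readings are tempting. A reader might infer that the design reaches 90% power only if about 83% of patients have the event. That figure needs a two-sided test together with the most severe of the three dilution models, and the paragraph states neither. The dilution is itself the doubtful step.

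A reader might also take the earlier study's results in the Discussion, "53.8% received antiviral therapy and 69.6% received antibiotics adjustment in multiplex PCR group", as event proportions and conclude that the trial is underpowered. Those are two treatment changes in one arm of another study. They may overlap, and neither is this trial's endpoint. Even used as proxies, undiluted and with 396 evaluable, they give 84% power at 53.8% and 92% at 69.6%. That does not show a general shortfall.

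**Conclusion.** The loss step is wrong as printed, and the correct figure is 223 per group (446 in total). The consequence is negligible: 3 patients per group and less than half a point of power.

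The 10% mNGS input sits badly with a design in which that test belongs to the Group II strategy, and its use is unexplained.

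The 90% power is unverifiable from the stated inputs, not refuted. With 400 evaluable patients it corresponds to an event proportion of about 64% (two-sided, undiluted), 76–83% (two-sided, with dilution) or 52–67% (one-sided 0.05, across the same cases). These ranges rest on Schoenfeld's formula, proportional hazards, equal allocation and the dilution models shown, none of which the article specifies beyond the 1:1 ratio. Overall this is a minor point.

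**What to change.** Change the text of Sample size calculation as follows.

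- **Loss.** Either write 200/0.9 = 223 per group (446 in total), or stay at 440 and state that about 198 per group (396) remain after 10% loss.
- **Additional mNGS.** Remove the 10% input, or say how it entered and why it is not already covered by a hazard ratio that compares the two strategies.
- **Events.** State that 90% power at HR 1.50 with two-sided α of 0.05 rests on about 256 events, and give the event proportion assumed. A short line of power by event proportion, labelled as an assumption, would do: about 81%, 88%, 92% and 95% at 50%, 60%, 70% and 80% for 396 evaluable patients.

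The cost is a few sentences. Staying at 440 needs no further enrolment; moving to 446 adds 6 patients. The power quoted may be a little below or above 90%, depending on the event proportion the sponsor can support.
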